## Abstract

Patients with severe mental disorders die on average 20 years prior to the general population. This mortality gap is mainly due to the higher prevalence of physical diseases and the adoption of unhealthy lifestyle behaviors.The LIFESTYLE trial aims to evaluate the efficacy of a new psychosocial group intervention (including psychoeducational, motivational, and problem-solving techniques) focused on healthy lifestyle behavior compared to a brief educational group intervention in a community sample of patients with severe mental disorders. The trial is a national-funded, multicentric, randomized controlled trial with blinded outcome assessments, which is carried out in six outpatient units of the Universities of Campania “Luigi Vanvitelli” in Naples, Bari, Genova, L'Aquila, Pisa, and Rome—Tor Vergata. All patients are assessed at the following time points: baseline (T0); 2 months post-randomization (T1); 4 months post-randomization (T2); 6 months post-randomization (T3); 12 months post-randomization (T4); and 24 months post-randomization (T5). T1 and T2 assessments include only anthropometric tests. The BMI, a reliable and feasible anthropometric parameter, has been selected as primary outcome. In particular, the mean value of BMI at 6 months from baseline (T3) will be evaluated through a Generalized Estimated Equation model. The work hypothesis is that the LIFESTYLE psychosocial group intervention will be more effective than the brief educational group intervention in reducing the BMI. We expect a mean difference between the two groups of at least one point (and standard deviation of two points) at BMI. Secondary outcomes are: the improvement in dietary patterns, in smoking habits, in sleeping habits, physical activity, personal and social functioning, severity of physical comorbidities, and adherence to medications. The expected sample size consists of 420 patients (70 patients for each of the six participating centers), and they are allocated with a 1:1 ratio randomization, stratified according to center, age, gender, and educational level. Heavy smoking, sedentary behavior, and unhealthy diet pattern are very frequent and are associated with a reduced life expectancy and higher levels of physical comorbidities in people with severe mental disorders. New interventions are needed and we hope that the LIFESTYLE protocol will help to fill this gap.

Trial registration number: 2015C7374S.

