### Patients' recruitment

Patients are being recruited in six outpatient units from the universities of Naples, Bari, Genova, L'Aquila, Pisa, and Rome—Tor Vergata.

Eligible patients are identified by their clinicians and referred to the LIFESTYLE research staff by phone, email, or in-person contact. After the patients have been contacted, a meeting is arranged at the outpatient clinic with the referring clinician and the LIFESTYLE staff. Verbal and written information about the project are provided. If the patient accepts to participate to the study, an informed consent form is signed and an appointment for baseline assessment is made. Once the informed consent is collected, the patient is formally enrolled in the study's protocol. Before starting the baseline assessment, the LIFESTYLE staff member contacts the statistician working at the Coordinating Center for obtaining the randomization code for patients' group allocation. The randomization procedure is stratified according to center, age, gender, and educational level with a 1:1 ratio. The treating psychiatrist will continue to provide the usual treatment to patients.

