## Anticipated results

### Primary outcome

BMI has been selected as primary outcome since it is a reliable and feasible anthropometric parameter, and it has already been considered in previous studies on lifestyle interventions (15, 16, 24). The primary outcome is the change of the BMI at 6 months post-randomization (T3). We expect a mean difference between the two groups of at least one point (and standard deviation of 2 points) at BMI. The work hypothesis is that the LIFESTYLE psychosocial group intervention will be more effective than the brief educational group intervention in reducing the BMI.

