## Statistical analyses

### Sample size and power calculation

A power analysis has been implemented in order to define the sample size needed to detect a significant BMI reduction (primary study's outcome) between the two groups. In particular, it has been estimated a sample size needed to observe a mean difference between the two groups of at least one point at the BMI (kg/m^2^) (with standard deviation of 2), with power set at 90% and a significant two-tailed alpha level of 0.05, based on previous studies on the same topic [e.g., (21, 23)].

Taking into account the multicenter design of the study, sample size has been adjusted for the Intercluster Correlation Coefficient (ICC), set at 0.030, and for the coefficient of variation of cluster sizes (COV), set at 0.400 (55). Therefore, the sample size consists of 348 patients (29 patients per arm in each center). Each center is expected to recruit 58 patients, rounded to 60. Moreover, previous trials evaluating the efficacy of interventions focused on physical activities and diet reported a drop-out rate of 15%; thus, the sample size has been rounded to 35 patients per arm for each center. Therefore, the expected sample size consists of 420 patients (70 patients for each participating center). This sample size has been considered feasible by all participating centers (Figure 1).

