The implementation of a generalized estimated equation model (GEE). The GEE provides an estimation of the longitudinal impact of the interventions on primary and secondary outcomes, controlling for confounders, such as physical comorbidities, severity of psychiatric symptoms, level of social functioning, quality of life, self-esteem, recovery style, support from social network. A generalized estimating equation model will be employed using the following outcomes variables: the BMI, the severity index of the Cumulative Illness Rating Scale, the abdominal circumference: plasma levels of glucose, insulin, triglycerides, and cholesterol levels (total, LDL, and HDL); systolic and diastolic blood pressure, and cigarettes smoked per day.The development of a Structural Equation Model (SEM) in order to identify possible mediators and moderators of the efficacy of the interventions, controlling for several confounders such as age, gender, severity of symptoms, BMI, etc. In particular, the variable “duration of the intervention” will be tested as one of the most relevant mediator or moderator for the efficacy of the interventions.The implementation of multivariable logistic regression models, in order to identify predictors of positive response for changing unhealthy behaviors. In particular, as regards the primary outcome, this will be transformed in binary variable (yes vs. no) using the reduction of at least 1 point at the BMI as threshold. The impact of possible predictors (e.g., having an healthy diet; walking at least 30min per day; quitting smoking) as well as confounders (such as age, gender, level of education, diagnosis, duration of the illness, type of pharmacological treatment received) will be tested in a logistic regression model.A subgroups analysis, according to the different diagnostic groups, in order to identify different profiles of efficacy of the interventions. The hypothesis is that patients suffering from affective disorders (both major depression and bipolar disorders) will report a higher improvement in the reduction of BMI and in changing their unhealthy lifestyle behaviors compared to patients with schizophrenia.

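### The primary outcome is mean BMI at T3 in the Abstract but change in BMI in the Methods; the GEE names no T3 contrast or baseline BMI, and SD 2 fits only a change or baseline-adjusted scale.

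*Protocol article*

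**What the plan says.** All references are to the protocol article.

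- **Abstract.** The primary quantity is a level at one visit: "In particular, the mean value of BMI at 6 months from baseline (T3) will be evaluated through a Generalized Estimated Equation model".
- **Primary outcome.** It is a change: "The primary outcome is the change of the BMI at 6 months post-randomization (T3").
- **Sample size and power calculation.** The target is a BMI reduction, sized to detect "a mean difference between the two groups of at least one point at the BMI", with SD 2, 90% power and two-sided alpha 0.05. The section does not say whether SD 2 is the SD of BMI at a visit, of change, or of a baseline-adjusted value.
- **Data analysis.** On the model itself: "The GEE provides an estimation of the longitudinal impact of the interventions on primary and secondary outcomes". It names no visit, contrast or arm-by-time term, although Table 3 schedules the anthropometric measures at all six visits from T0 to T5. The adjustment is described as "controlling for confounders, such as physical comorbidities, severity of psychiatric symptoms, level of social functioning, quality of life, self-esteem, recovery style, support from social network".
- **Patients' recruitment.** "The randomization procedure is stratified according to center, age, gender, and educational level with a 1:1 ratio". None of these four factors is among the GEE examples, nor is baseline BMI. Age, gender and BMI are named for the structural equation model, and age, gender and education for the logistic responder model. Centre is in no covariate list.
- **Patients' inclusion criteria.** BMI of at least 25, with no upper limit.

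**The concern.** A level at T3 and a change to T3 are different outcome variables. Randomisation gives them the same expected arm difference, so the choice does not alter what is estimated. It does alter the standard error, because an unadjusted level carries all the between-patient spread in BMI that was present at entry.

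The trial was sized with SD 2. If that SD belongs to change or to a baseline-adjusted value, an analyst who follows the Abstract literally would run a comparison that the sample size was not built for. The Data analysis section does not settle the matter, because it names neither the T3 contrast nor baseline BMI. Baseline BMI is likely to be the strongest single predictor of T3 BMI, yet the examples name quality of life and recovery style and not this variable. The stratification factors, which an analysis would normally carry because the randomisation used them, are also absent. What is at stake is the precision of the primary test and whether its form is fixed before the data are seen.

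**Working it through.** **1. The plan's own figure.** Inputs from Sample size and power calculation: difference 1, SD 2, alpha 0.05 two-sided, power 90%, ICC 0.030, coefficient of variation of cluster size 0.400, 29 per arm per centre, six centres.

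- Without clustering: n = 2 × 2² × (1.960 + 1.2816)² / 1² = 84.06, so 85 per arm (86 with the noncentral t).
- Design effect, treating each centre-arm as a cluster of m: DE = 1 + ((1 + 0.4²)m − 1) × 0.03. This is 1.979 at m = 29 and 2.014 at m = 30.
- 86 × 1.979 = 170.2 per arm (340 in all); 86 × 2.014 = 173.2 per arm (346 in all). The plan states 348.
- Power at 174 per arm: Φ(1 / (2 × √(2 × 1.979/174)) − 1.96) = 91.2%.
- Dropout: 29/0.85 = 34.1, rounded up to 35 per arm per centre, which gives 420.

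The stated size is therefore reproduced for an outcome whose SD is 2.

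**2. Which scale has SD 2?** The documents give no SD of BMI at a single visit. With raw SD S, equal at baseline and T3, and baseline-to-T3 correlation r, the SD of change is S√(2(1 − r)) and the baseline-adjusted SD is S√(1 − r²). Setting the SD of change to 2 gives r = 1 − 2/S²: 0.78, 0.88, 0.92 and 0.94 for S = 3, 4, 5 and 6. The baseline-adjusted SD is then 1.89 to 1.97. SD 2 is thus a coherent figure for either of these scales.

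For a raw level, take as an illustration an exponential distribution starting at 25 with SD 2. Its mean is 27, and the share above 30 is exp(−5/2) = 8%. That is an unusually narrow cohort for an entry criterion with no ceiling.

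**3. Power if unadjusted T3 levels were compared.** Power = Φ(1 / (S√(2·DE/n)) − 1.96) for a 1-point difference. S is an assumption and is shown as a range. n = 174 is the evaluable target; n = 178 is 420 × 0.85 / 2, rounded down. DE is 1.979, or 1 for no design effect.

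| Assumed raw SD | n = 174, no DE | n = 178, no DE | n = 174, DE 1.979 | n = 178, DE 1.979 |
|---|---|---|---|---|
| 2 | 99.7% | 99.7% | 91.2% | 91.8% |
| 3 | 87.5% | 88.2% | 59.9% | 60.8% |
| 4 | 64.5% | 65.5% | 38.1% | 38.8% |
| 5 | 46.2% | 47.1% | 26.3% | 26.8% |
| 6 | 34.3% | 34.9% | 19.6% | 20.0% |

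The largest SD that keeps 90% power at 174 per arm is 1 / (3.2416 × √(2·DE/174)) = 2.05 with the design effect and 2.88 without it. Because patients are randomised within centre, the design effect is probably conservative, so the columns without it are the favourable bound.

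**4. The covariates.** Setting the Patients' recruitment factors against the GEE examples gives no overlap: none of centre, age, gender and education is named. In a linear model with stratified allocation, leaving out prognostic stratification factors mainly makes the standard error too large. It costs precision and does not inflate false positives. The documents give no figure from which the size of this loss could be computed.

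**The case against.** The strongest reply is that the body text largely settles the scale. Both Methods sections speak of change or reduction, and only one sentence of the Abstract speaks of a mean value, next to a hypothesis about reducing BMI. Variable, visit and hypothesised difference agree throughout. The covariates are offered as examples, so absence is not exclusion, and a condensed article may leave model detail to an analysis plan. If T0 is part of the GEE response and the arm-by-time contrast at T3 is used, baseline variation is removed without a baseline covariate.

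Much of this stands, and it rules out several stronger readings:

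- **Three competing primary outcomes.** A reader might count the GEE's longitudinal impact as a third definition. It describes an analysis, not an outcome.
- **Dilution by pooling visits.** Averaging a linear onset (0.33, 0.67 and 1 at T1 to T3) would give 0.67. The documents state neither the averaging nor the linear onset, and the Abstract ties the GEE to T3.
- **Most of the power is lost.** Without a design effect, more than half of the 99.7% is lost only at raw SDs of 5 and 6. At SD 3 the figure is still about 88%.
- **The sample size is wrong.** It reproduces.

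What the reply does not remove is that the Abstract and the Methods disagree in print, that nothing says the T3 contrast or T0 in the response will be used, and that SD 2 is attached to no named scale.

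**Conclusion.** The point holds as an inconsistency in how the primary analysis is fixed. The Abstract names a level at T3, the Methods name a change, the GEE description names no T3 contrast, and its examples omit baseline BMI and the four stratification factors. The arm difference being estimated is the same; the precision is not.

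On the unadjusted-level reading, power would be about 88% to 35% for raw SDs of 3 to 6 without a design effect, or about 60% to 20% with the plan's own adjustment, against a stated 90%. These figures rest on assumed raw SDs, a true difference of 1 point and 174 to 178 evaluable patients per arm. That SD 2 belongs to change or to a baseline-adjusted value is an inference. It is supported by the reduction wording in the sample-size section and by entry with no upper BMI limit, but it is not stated. A reader might also infer inflated type I error from the missing stratification factors; the expected effect is wider standard errors instead.

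**What to change.** State one primary estimate in the Abstract, Primary outcome and Data analysis sections: the between-arm difference in BMI at T3 adjusted for baseline BMI, taken as the T3 contrast from the GEE. Name centre, age, gender and educational level as covariates in that model. Label BMI contrasts at the other visits as secondary. In Sample size and power calculation, say that SD 2 is the SD of change or the baseline-adjusted SD; 348 and 420 then need no alteration.

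The cost is wording only. Baseline BMI is on the T0 anthropometric schedule; age, gender and education are on the baseline socio-demographic schedule; and centre is known for every patient. The adjustment gains precision over the covariates now named, and it puts the analysis on the scale that SD 2 fits.

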## Introduction

In the last decade, the need to improve physical health in patients with severe mental disorders, namely schizophrenia, major depression, and bipolar disorders (1), has been repeatedly highlighted by several international scientific bodies and reported in several guidelines (2–6). Nevertheless, physical health of people with several mental disorders is often neglected by the patients themselves, as well as by their caregivers and mental health professionals (1).

Patients with severe mental disorders die on average 20 years prior to the general population (7). In patients with severe mental disorders, cardiovascular diseases, and other physical diseases contribute significantly to the reduced life expectancy, even if more than other “unnatural” causes, such as accidents or suicide (8–10). Among the relevant and modifiable factors for explaining the high cardiovascular morbidity and mortality of patients with severe mental disorders two factors have been repeatedly recognized: the poor access to prevention and screening programmes and the adoption of unhealthy lifestyle behaviors (11). It is unacceptable that life expectancy, which is substantially grown in developed countries in the general population, remains so short in people with schizophrenia and other severe mental disorders (12, 13).

Recently, it has been reported that receiving a diagnosis of schizophrenia is associated with at least 13–15 years of potential life lost; therefore, there is the need to develop and implement individual-based and/or community-level interventions in order to reduce this excess mortality in people with severe mental disorders (1, 14).

Interventions could improve global health and well-being in people with severe mental illness by modifying their unhealthy lifestyle behaviors. According to a recent review, people with mental disorders are more sedentary than the general population (matched for gender and age) and are significantly less physically active. Moreover, at least 50% of people with severe mental illness do not meet the general recommendation of performing at least 150 min of moderate physical activity per week (1). Moreover, patients with severe mental disorders have unhealthy diet pattern, with a low intake in fruit and fiber and a high intake of junk food (15, 16). Compared with the general population, people with mental disorders have a higher probability of being heavy smokers (i.e., more than two packs/day) (17–19).

Increasing the levels of physical activity, improving dietary patterns, and reducing smoking habits of people with severe mental disorder may represent a global health challenge and a public health priority.

On these premises, several psychosocial interventions—including behavioral, educational, and psychological components—have been developed worldwide for addressing these needs (20–25). In particular, some interventions have been specifically focused on improving dietary patterns [e.g., (24)] or smoking habits [e.g., (26)] or on physical inactivity, unhealthy dietary habits, and smoking [e.g., (22, 23)]. These lifestyle psychosocial interventions—that are different in format, setting, duration, and involved professionals—have been found to be effective in improving patients' physical health.

However, several aspects have been identified as critical for the provision of lifestyle interventions in the clinical routine care. The optimal duration of the intervention; the involvement of a multidisciplinary team: the evaluation of cost/effectiveness ratio: the feasibility of the intervention in the real word practice are some of the most crucial ones. Recently, Speyer et al. (22, 23) found that the CHANGE trial was not superior to treatment as usual in reducing cardiovascular risk in patients with schizophrenia spectrum disorders and abdominal obesity, but more data are needed for patients with other severe mental disorders.

Moreover, there is the need to understand if these interventions actually reduce the mortality gap, and they should be evaluated in routine care, in large samples and in the long term (25). In order to assess the efficacy and the feasibility of these lifestyle interventions, an easy, reliable, and affordable anthropometric parameter, as the Body Mass Index (BMI) should be selected (15, 16, 24). Under these premises, a multicentric collaborative study, coordinated by the Department of Psychiatry of the University of Campania “Luigi Vanvitelli in Naples, Italy” and funded by the Italian Ministry of Education, Universities and Research, has been proposed for evaluating the efficacy and effectiveness of new psychosocial group interventions targeted on lifestyle in a real-world sample of patients with severe mental disorders, in terms of reduction of BMI.

## Aims

The LIFESTYLE trial aims to evaluate the efficacy of a new psychosocial group intervention focused on healthy lifestyle behaviors compared to a psychoeducational brief group intervention in a community sample of patients with severe mental disorders on several variables including BMI, comorbidity index, smoking habits, and dietary patterns.

The secondary aims of the trial are: (1) to identify predictive factors associated with poor response to the interventions; (2) to define the role of mediators and moderators for the efficacy of the interventions; (3) to describe differences according to diagnostic groups in terms of improvement of lifestyle behaviors; (4) to evaluate the long-term effects of the interventions and their cost-effectiveness; (5) to develop guidelines for improving healthy lifestyle in people with severe mental disorders in the clinical routine care.

## Methods

### Design

The LIFESTYLE trial is a national-funded, multicentric, randomized controlled trial with blinded outcome assessments. The project has been funded by a grant of the Italian Ministry of Education, Universities and Research within the framework of the “Progetti di Rilevante Interesse Nazionale (PRIN) — year 2015”. It is a multicentric study involving the outpatient units of the University of Campania “Luigi Vanvitelli” in Naples, University of Bari, University of Genova, University of L'Aquila, University of Pisa, and University of Rome—Tor Vergata. The University of Campania “Luigi Vanvitelli” in Naples is the coordinating center, which has originally conceived the study's idea and design.

This is a randomized head-to-head comparison trial with two parallel arms for evaluating the efficacy and effectiveness of psychosocial group interventions in improving lifestyle behaviors in patients with severe mental disorders. The two interventions have been developed by the research staff and are both focused on the improvement of lifestyle behaviors.

### Patients' recruitment

Patients are being recruited in six outpatient units from the universities of Naples, Bari, Genova, L'Aquila, Pisa, and Rome—Tor Vergata.

Eligible patients are identified by their clinicians and referred to the LIFESTYLE research staff by phone, email, or in-person contact. After the patients have been contacted, a meeting is arranged at the outpatient clinic with the referring clinician and the LIFESTYLE staff. Verbal and written information about the project are provided. If the patient accepts to participate to the study, an informed consent form is signed and an appointment for baseline assessment is made. Once the informed consent is collected, the patient is formally enrolled in the study's protocol. Before starting the baseline assessment, the LIFESTYLE staff member contacts the statistician working at the Coordinating Center for obtaining the randomization code for patients' group allocation. The randomization procedure is stratified according to center, age, gender, and educational level with a 1:1 ratio. The treating psychiatrist will continue to provide the usual treatment to patients.

